### Nested qualitative sub-study

We will invite selected volunteers to focus group meetings and participants to individual interviews. Using an interview guideline, they will be asked to discuss their experiences with respect to positive aspects and shortcomings of the intervention. A special focus will be on effects of the intervention on physical and psychosocial wellbeing and quality of life as well as specific challenges encountered by either volunteers or participants. All interviews will be audiotaped and transcribed verbatim. The resulting text will be analysed qualitatively by means of a text analysis.

### Statistical analysis

#### Sample size

Sample size calculation was carried out based on expected effects regarding the primary outcome (physical function measured by the Short Physical Performance Battery [13] after 6 months of intervention (T1). A change of 1 point has been shown to be clinically relevant (e.g. predictive of future hospitalisation, health improvement and mortality) [33]. The standard deviation in comparable samples has ranged between 2.6 and 2.8 points [30, 31]. With a conservative approach, we assumed the higher standard deviation (2.8) for our calculation. In an analysis of covariance (including baseline values of the primary outcome), with an R-square of 0.5 for the covariate and a power of 95% (1-β), sample sizes of *n*=103 will be required for each of the two groups. The total sample of 206 participants achieves 95% power to detect differences among the means using an F test with a 5% significance level. The size of the variation in the means is represented by their standard deviation, which is 0.50. The common standard deviation within a group is assumed to be 2.8.

In our pilot study [12] conducted in nursing homes, we experienced a loss of 28% during the 6 months intervention period mainly due to death and hospitalisation. From our experience, the loss of participants recruited in primary care practices will be lower. A British primary care and community based study, which examined a complex nurse-delivered intervention with self-paced exercises and therefore people who are likely to be physically healthier (compared to our participants), experienced a loss of 6% during 3 months [9]. Considering that we are now also recruiting participants in community settings (living at home, primary care) and following a conservative approach, we set the expected loss during the intervention period to 40% (mainly due to death and hospitalisation). Assuming a loss of 40% during the 6 months of intervention we will need a total sample of *n*=345 to achieve adequate power of 95% at our primary endpoint. This will also enable us to achieve enough power for the analyses of secondary endpoints. The study centre Marburg will aim to recruit 230 persons from the community setting and the study centre Witten 115 from nursing homes.

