#### Data analysis

At T1, we will apply an analysis of covariance of the primary outcome physical function (SPPB scores). This outcome will be used to analyse the difference between the intervention and control group. In case of non-normally distributed data, we will apply a nonparametric covariance model [34]. The secondary outcomes will be evaluated with ANCOVAs, t-tests or distribution independent Mann-Whitney U-Tests. To compare the number of deaths, events leading to discontinuation of the intervention, falls requiring medical attention, and hospital treatments, we will either calculate a χ2-test, Fisher exact test for binary variables or conduct a log-rank-test. Since the number of falls or falling in general has shown to depend on fear of falling and the amount of physical activity, we will perform a mediator analysis to correctly identify the effect of our intervention on falling [35].

Furthermore, we will perform exploratory analyses (multifactorial ANCOVAs and in case of non-normally distributed data adjusted rank transform tests [36]) and dichotomise and evaluate whether the participants in the subgroups setting (community setting, nursing home), sex, rural/urban setting, frailty, and baseline SPPB score show different results in our primary outcome SPPB or in secondary outcomes. We will perform this analysis at T1 and T2.

The evaluation of the intervention will be performed as intention-to-treat (ITT). The ITT analysis will include all randomised participants irrespective of the actual performance of the intervention. In case a participant decides to withdraw consent, we will ask for a final evaluation.

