#### Missing data

If the T1 or T2 evaluation of a participant cannot be performed, the research assistant will decide whether an informative (death, admission) or non-informative event (e.g. moving to another municipality) has caused the evaluation to be missed. Information on reasons for missing the T1 or T2 evaluation will be obtained from participants’ families, general practitioners or nursing teams.

Depending on this categorisation, the following methods for analysis taking into account missing values will be used: 1) informative missing: not able to attend [examination] because of previous nursing home admission, hospital admission or death - tied worst rank score method will be assigned a SPPB Score = 0. For secondary outcomes, we will proceed in a similar fashion. In the analysis, we will apply the worst-rank score analysis [37]. It considers only the relative ordering of the values and applies the minimum variance linear or best linear estimator. For secondary outcomes, we will proceed in a similar fashion. 2) In case of non-informative missing (not able to attend because participant moved to another place without one of the conditions mentioned above), we will proceed with multiple imputation. In case of non-normally distributed data, we apply a nearest neighbour multiple imputation approach to estimate the proportion of each then categorised variable [38]. For secondary outcomes, we will proceed in a similar fashion.

We will also perform an additional per-protocol analysis, which will only include participants whose follow–up examination has taken place at the designated time (6 months after baseline or follow-up ± 2 weeks). Individuals of the intervention group participating in less than 25% of the scheduled walks will be excluded in the per-protocol analysis.

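### The stated 95% power belongs to a completers-only ANCOVA, not to the planned intention-to-treat analysis that scores death and admission as SPPB 0

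*Protocol article*

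**What the plan says.** The Sample size section calculates for an ANCOVA on SPPB at six months (T1), "with an R-square of 0.5 for the covariate and a power of 95% (1-β". The effect is given as a spread of the group means: "The size of the variation in the means is represented by their standard deviation, which is 0.50". For two equal groups that is a difference of 1 point. The within-group SD is 2.8. The result is 103 per group: "The total sample of 206 participants achieves 95% power to detect differences among the means using an F test with a 5% significance level".

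The section then allows for attrition: "we set the expected loss during the intervention period to 40% (mainly due to death and hospitalisation". This raises the total to 345. It adds of the secondary outcomes: "This will also enable us to achieve enough power for the analyses of secondary endpoints".

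The Data analysis section defines the analysis set: "The ITT analysis will include all randomised participants irrespective of the actual performance of the intervention". The Missing data section divides missed visits into two kinds. For those caused by death, hospital admission or nursing-home admission, "tied worst rank score method will be assigned a SPPB Score = 0", followed by a worst-rank analysis. Only non-informative losses, such as moving away, are multiply imputed.

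**The concern.** Dividing 206 by 0.6 makes sense only if the lost 40% leave the analysis. Under the analysis sections most of them do not leave. The sample size text names death and hospitalisation as the main causes of loss, and those are the events that lead to a score of 0 when they cause T1 to be missed. The same participants are thus absent when power is calculated and present as zeros when the primary outcome is tested.

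The calculation leaves out three consequences. The between-group difference is diluted, because participants scored 0 in both arms contribute no difference. The variance gains a large spike at the bottom of the scale. The baseline score explains less of the outcome, and the rank analysis has a large block of ties.

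At stake is how a null result is read. Against a 95% claim it would look like strong evidence that a 1-point benefit is absent. The reassurance drawn from a generous loss allowance is also misplaced: with equal loss by arm, more informative loss means less power.

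**Working it through.** **1. The plan's own figures.** Residual SD = 2.8 × √(1 − 0.5) = 1.98. With 103 per group, the noncentrality is 1 / (1.98 × √(2/103)) = 3.62, which gives 95.0% power at two-sided 5%. Inflation: 206 / 0.6 = 343.3, consistent with 345. Conversely, 345 × 0.6 = 207 completers, again 95%. The stated figures reproduce, as a completers-only ANCOVA.

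**2. Inputs for the planned analysis.**
- From the Sample size section: 345 randomised, SD 2.8, R-square 0.5, difference 1 point, 40% loss.
- Assumed, because the documents do not give them: equal loss by arm; the 1 point applies to completers; control-arm completers' mean SPPB at T1 of 5, 6 or 7 (baseline eligibility lies above 2 or 3 and below 9); share s of the loss that is informative of 60%, 80% or 100%.
- Non-informative losses are left out as a stand-in for multiple imputation.

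**3. Formula.** With loss L:
- Analysed N = 345 × (1 − L(1 − s))
- Proportion of zeros q = Ls / (1 − L(1 − s))
- Expected difference = (1 − q) × 1
- Residual variance = (1 − q) × 2.8² + q(1 − q) × (average of the two squared arm means) − (1 − q)² × 0.5 × 2.8²
- Noncentrality = difference / (SD × √(4/N))

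**4. Worked case.** L = 40%, s = 100%, means 6 and 7: q = 0.40 and difference 0.60. Variance = 0.6 × 7.84 + 0.24 × 42.5 − 0.36 × 3.92 = 4.70 + 10.20 − 1.41 = 13.49, so SD = 3.67. Noncentrality = 0.60 / (3.67 × √(4/345)) = 1.52, giving power of about 33%.

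**5. All cases at 40% loss, ANCOVA with zeros.** SD and power are listed for control means of 5 / 6 / 7.

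| Informative share | N | Zeros | Difference | Residual SD | Power |
|---|---|---|---|---|---|
| 100% | 345 | 40% | 0.60 | 3.26 / 3.67 / 4.10 | 40 / 33 / 27% |
| 80% | 317 | 35% | 0.65 | 3.22 / 3.62 / 4.03 | 44 / 36 / 30% |
| 60% | 290 | 29% | 0.71 | 3.13 / 3.50 / 3.89 | 49 / 41 / 34% |

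Simulated worst-rank tests (Mann-Whitney and rank ANCOVA) give about 21–37% over the same cases. Across methods and simulation variants, a fair range is roughly 20–55%. Imputing the non-informative losses as non-zero scores would raise the top corner somewhat. Even if every imputed score counted as observed (N = 345, 24% zeros, difference 0.76, SD 3.04, noncentrality 2.32), power would be 64%.

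**6. Lower loss, same assumptions, ANCOVA.**
- 28% (the pilot's rate): about 41–68%.
- 17%: about 61–86%. This blends the quoted rates, with the British study's 6% in 3 months doubled: (115 × 28% + 230 × 12%) / 345 = 17.3%.
- 10%: about 80–95%.

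Rank tests are mostly somewhat lower. Rank ANCOVA can exceed ANCOVA with zeros when the assumed mean is high and loss is low.

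**7. Unequal loss.** With 40% informative loss in controls and a control mean of 6, simulated power is 33–44% if the intervention arm loses 38%, 57–67% at 35%, and 86–92% at 30%.

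**The case against.** Several points on the other side have force.

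- **The 40% is a deliberately high planning value.** The nursing-home pilot lost 28%, and 230 of the 345 are to come from the community, where lower loss is expected. At 10–17% the shortfall is much smaller. This stands, and it is why power should be shown over a range of loss rates.
- **Not every loss becomes a zero.** The text says that death and hospitalisation are the main causes, not the only ones. The score of 0 applies only when the T1 visit cannot be done for those reasons. Assessors visit people at home or in care homes, and those who withdraw are asked for a final evaluation. This stands too, hence the 60–100% range.
- **The 1 point might be meant for the composite as analysed.** Putting a difference of 1.0 against the extreme SDs in the table gives noncentrality 1 / (4.10 × √(4/345)) = 2.26 and 1 / (3.13 × √(4/290)) = 2.72, or power of about 62% and 77%. That is roughly 60–80%, still short of 95%.
- **A worst-rank composite also gains from fewer deaths or admissions.** True, and the Aims section does ask about hospitalisation and mortality. But power nears 90% only with a drop of about 10 percentage points, and the sample size text assumes no such effect.
- **The exact worst-rank estimator and nonparametric covariance model rest on cited sources that are not shown.** The tests used here are therefore stand-ins.

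A reader might go further and infer one definite figure, such as a one-in-three chance of success. The documents do not support that: it would require fixing the mean SPPB, the informative share and equal loss by arm, none of which they state. Nor should a reader infer an arithmetic slip, because both 206 and 345 reproduce.

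**Conclusion.** The mismatch is real and can be read directly from the text: the power statement assumes that lost participants disappear, while the primary analysis keeps most of them at the bottom of the scale. At the plan's own 40% loss, with equal loss by arm and the other assumptions in step 2 of the working, power is roughly 20–55%. No equal-loss case examined at 40%, including the composite reading of the 1 point, reaches 95%. Only at about 10% loss does the upper end of the range come close. The size depends on inputs that the documents leave open; the direction does not, unless the intervention also reduces death or admission.

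The claim of sufficient power for secondary endpoints has no support in the text. It gives no effect size, event rate or variance for any of them, and their informative losses are to be handled in a similar way.

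**What to change.** Keep 345 randomised. In the Sample size section:

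- Label the 95% as applying to a completers-only ANCOVA with 206 analysed.
- Give the power of the planned worst-score intention-to-treat analysis as a short table over informative-loss rates of 10–40%. State the assumed mean SPPB, the informative share, and equal or unequal loss by arm.
- State that the effect tested is on the composite of SPPB and death or admission.
- Stop describing the 40% as conservative for power.
- Delete the sentence on secondary endpoints, or replace it with detectable differences.

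The cost is protocol or SAP wording and a short simulation. No extra participants are needed. The downside is that the stated power becomes less favourable.

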### Aims

Our research questions are:
Compared to controls, does volunteer-supported walking improve physical function and quality of life as well as lower fear of falling? Furthermore, improves supported walking the cognitive executive function and the general physical activity? [Effectiveness]Compared to controls, does volunteer-support walking increase the rate of falls needing medical attention, rate of admissions to hospital, duration of hospitalisations and mortality? [Safety]Compared to controls, does supported walking have an impact on the frequency and duration of hospitalisations and/or mortality? [effectiveness, safety]

Finally, we explore whether the intervention can be successfully implemented into existing community services.

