### Outcomes

We expect the intervention to impact upon muscle strength, balance and ability to walk. We therefore chose the Short Physical Performance Battery as the main outcome of the study. SPPB scores have been shown to be associated with disability in mobility and activities of daily living [26–28], future hospitalisation [29], health improvement [30] and mortality [30–32]. For these simple measures of performance, the SPPB shows a good reliability and validity [27].

As secondary outcomes we will evaluate quality of life (EQ-5D-5L), fear of falling (FES-I), physical activity (activity diary), cognitive executive function (clock drawing test), falls requiring medical attention, hospitalisation and death.

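### The statement that the sample size gives enough power for the secondary endpoints does not follow from the SPPB calculation and is unsupported for treated falls, hospitalisation and death

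*Protocol article*

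**What the plan says.** The Sample size section of the protocol article derives the number of participants from SPPB at T1 alone. The inputs are a 1-point difference, a standard deviation of 2.8 and an analysis of covariance "with an R-square of 0.5 for the covariate and a power of 95% (1-β), sample sizes of" 103 per group, "using an F test with a 5% significance level". Allowing for 40% loss gives 345 to be randomised. The section then states: "This will also enable us to achieve enough power for the analyses of secondary endpoints".

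The Outcomes section counts "falls requiring medical attention, hospitalisation and death" among the secondary outcomes, next to quality of life, fear of falling, physical activity and the clock-drawing test. The safety question under Aims asks whether the intervention raises the "rate of falls needing medical attention, rate of admissions to hospital, duration of hospitalisations and mortality". For such events the Data analysis section says that "we will either calculate a χ2-test, Fisher exact test for binary variables or conduct a log-rank-test". It states no margin.

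**The concern.** The power sentence is an affirmative claim about every secondary endpoint, so it is not a detail left to an analysis plan. Nothing in the article supports it for the event outcomes. The SPPB calculation gains half of its variance from the baseline covariate, and the chi-square, Fisher and log-rank tests have no such gain. Power for events depends on how many occur, and the article gives no rate for any of them.

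The safety question is answered by tests of difference. If an event is uncommon, a non-significant result is compatible with a large increase. A reader who has been told that power was sufficient could give such a result more weight than it can bear. There is also a mismatch of quantity. Aims asks about rates of falls and admissions, whereas the named tests compare proportions or times to a first event and discard repeat events.

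**Working it through.** **Inputs from the article.** SPPB difference 1.0 (standard deviation of the two means 0.50), SD 2.8, R-square 0.5, power 95%, 5% level, 1:1 allocation, 40% loss, 345 randomised, and intention-to-treat analysis of all randomised.

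**Assumed.** Control risks, a relative risk of 1.5, the same 5% two-sided level for events, and event status known for all randomised participants.

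**Step 1: the plan's own figure.** Residual variance = 2.8² × (1 − 0.5) = 3.92. By the normal approximation, n per arm = 2 × (1.960 + 1.645)² × 3.92 / 1² = 101.9, so 102. The noncentral F distribution gives 95.0% power at 103 per arm, so the stated 103 is right. Loss: 206 / 0.60 = 343.3, so 344 against the stated 345, a trivial difference. The primary calculation reproduces.

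**Step 2: power for an event.** Per arm, 345 / 2 ≈ 172. With control risk p, intervention risk q = 1.5p and mean risk m = (p + q)/2:

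Power = Φ( [ (q − p) − 1.96 × √(2m(1 − m)/n) ] / √( [p(1 − p) + q(1 − q)]/n ) )

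Example, p = 0.10, q = 0.15, m = 0.125: the null standard error is √(2 × 0.125 × 0.875/172) = 0.03566 and the alternative standard error is √((0.09 + 0.1275)/172) = 0.03556. Then (0.05 − 1.96 × 0.03566)/0.03556 = −0.56, and Φ(−0.56) = 0.29.

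The log-rank column uses Φ(√E × ln 1.5 / 2 − 1.96), with E = 172 × (p + q) events. It takes 1.5 as a hazard ratio, which is a smaller effect than a risk ratio of 1.5 when events are common. The last column is the relative risk detectable with 80% power by the chi-square formula.

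| Assumed control risk | Chi-square, RR 1.5 | Fisher exact, RR 1.5 | Log-rank, HR 1.5 | Detectable RR, 80% power |
|---|---|---|---|---|
| 5% | 16% | not computed | 15% | 2.76 |
| 10% | 29% | 24% | 26% | 2.09 |
| 15% | 43% | 38% | 37% | 1.82 |
| 20% | 57% | 53% | 47% | 1.67 |
| 28% | 78% | 74% | 60% | 1.51 |
| 40% | 96% | 95% | 76% | 1.38 |

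A log-rank test for a hazard ratio of 1.5 needs 191 events for 80% power.

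**Step 3: what a null result could exclude.** If both arms had a true risk of 10%, the standard error of the log relative risk would be √(2 × 0.90/(172 × 0.10)) = 0.323. The expected 95% interval is exp(±1.96 × 0.323), or 0.53 to 1.89. A near-doubling would not be excluded.

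**Step 4: continuous secondary outcomes.** At 103 per arm with no covariate, power is 82% for a standardised difference of 0.4 and 95% for 0.5. The difference detectable with 80% power is about (1.96 + 0.84) × √(2/103) = 0.39.

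**The case against.** The strongest reply is that the article's own figures point to common events. It reports 28% loss in the pilot and plans for 40%, both attributed mainly to death and hospitalisation. At control risks of that size, chi-square power for a 50% rise is 78% and 96%. If the two figures are instead averages over both arms (control risks of 0.28/1.25 = 22.4% and 0.40/1.25 = 32%), it is about 64% and 86%. This stands for hospitalisation, which can be commoner than loss because not every admission ends participation, and for a combined event.

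It does not rescue the sentence as a whole. The figures are losses from all causes, not rates of a single event. Treated falls are not named as a main cause of loss. Death alone cannot exceed the total loss. The 28% comes from nursing homes, which supply 115 of the 345, and the article expects lower loss in primary care. The 40% is described as conservative.

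Four stronger readings are tempting, and the documents do not support them:

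- *The design has about 30% to 57% power for a 50% rise.* That range results from assuming control risks of 10% to 20%, which the article does not give. Power may be lower for a rarer event and higher for a commoner one.
- *The trial will report a null test as safety.* No section says so. The wording creates the risk and goes no further.
- *The power sentence is wrong for all secondary endpoints.* Step 4 shows that it can be right for continuous outcomes with a moderate effect.
- *The event analyses will have only 103 per arm.* That is the SPPB completer number. Events are to be analysed in all randomised participants, and families, general practitioners or nursing teams are asked why a visit was missed.

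It can also be said that the named tests are valid and that count models are commonly left to an analysis plan. The tests are valid for whether, or when, a first event occurs. They do not estimate the rates that Aims asks about.

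**Conclusion.** The point holds in limited form. The sample size for the primary endpoint is correct. The general power claim attached to it does not follow from that calculation and is unsupported for treated falls, hospitalisation and death. For any event with a control risk of about 20% or less, chi-square power for a relative risk of 1.5 is below 60%, and only relative risks of about 1.67 or more are detectable with 80% power. Low power is not shown for hospitalisation, a combined event, or continuous outcomes with a standardised difference of about 0.4 or more. These figures rest on 172 per arm, a two-sided 5% level, complete event ascertainment and control risks that are assumed throughout. The correction is worth making before results are known, because it governs how a non-significant safety comparison may be read.

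**What to change.** 1. In the Sample size section, limit the power sentence to the continuous secondary outcomes and state the detectable standardised difference (about 0.39 with 80% power at 103 per arm and no covariate).
2. For treated falls, hospitalisation and death, state the assumed control risk and the relative risk detectable at the planned number, as in the last column of the table.
3. In the Data analysis section, analyse treated falls and admissions as counts with a negative binomial model, with log time at risk as offset and setting (the randomisation stratum) as covariate. Report the rate ratio with its 95% confidence interval. Keep the log-rank test for death and add an effect estimate with its 95% confidence interval.
4. State that a non-significant difference will not be taken as evidence of safety.

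Table 1 already lists the dates of treated falls and of hospital admission and discharge, so no new data are needed. The cost is a less favourable power statement and slightly more analysis work. The number randomised does not change.
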